## Abstract

**Introduction:**

The COVID-19 pandemic exposed people to significant and prolonged stress. The psychosocial impacts of the pandemic have been well recognised and reported in high-income countries (HICs) but it is important to understand the unique challenges posed by COVID-19 in low- and middle-income countries (LMICs) where limited international comparisons have been undertaken. This protocol was therefore devised to study the psychosocial impacts of the COVID-19 pandemic in seven LMICs using scales that had been designed for or translated for this purpose.

**Methods and analysis:**

This cross-sectional study uses an online survey to administer a novel COVID Psychosocial Impacts Scale (CPIS) alongside established measures of psychological distress, post-traumatic stress, well-being and post-traumatic growth in the appropriate language. Participants will include adults aged 18 years and above, recruited from Indonesia, Iraq, Iran, Malaysia, Pakistan, Somalia and Turkey, with a pragmatic target sample size of 500 in each country.

Data will be analysed descriptively on sociodemographic and study variables. In addition, CPIS will be analysed psychometrically (for reliability and validity) to assess the suitability of use in a given context. Finally, within-subjects and between-subjects analyses will be carried out using multi-level mixed-effect models to examine associations between key sociodemographic and study variables.

**Ethics and dissemination:**

Ethical approval was granted by the Human Ethics Committee, University of Otago, New Zealand (Ref. No. 21/102). In addition, international collaborators obtained local authorisation or ethical approval in their respective host universities before data collection commenced.

Participants will give informed consent before taking part. Data will be collected and stored securely on the University of Otago, New Zealand Qualtrics platform using an auto-generated non-identifiable letter-number string. Data will be available on reasonable request. Findings will be disseminated by publications in scientific journals and/or conference presentations.

**Trial registration number:**

NCT05052333.

Strengths and limitations of this studyThis cross-sectional observational study will make a significant contribution to understanding the psychosocial impacts of the COVID-19 pandemic in seven low- and middle-income countries with different pandemic impacts.This study will quantify psychometric measures in countries where there is currently limited access to newly developed scales relating to COVID-19 and associated measures of psychological distress, well-being and post-traumatic growth in appropriate languages.The findings will provide psychometric information on the novel COVID Psychosocial Impacts Scale (CPIS) in differing pandemic contexts.There are limitations associated with selective recruitment and response rate in this study; which may limit the generalisability of the findings and comparability between groups.

## Introduction

COVID-19 was identified as an infectious disease by the World Health Organization (WHO) on 11 February 2020.^1^ This new virus rapidly spread and was declared an international public health emergency on 30 January 2020 and a pandemic on 11 March 2020.^1^ As of 31 January 2023, there have been 753 497 572 confirmed cases of COVID-19 including 6 813 301 deaths reported by WHO^2^; and likely many more as a result of under-reporting.^3^ The COVID-19 pandemic has been complex in its origin, spread, impacts and consequences. Specifically, COVID-19 exposed people to significant and prolonged stress from often overlapping concerns like health consequences of COVID-19, impacts of public health restrictions (e.g., lockdowns, social distancing, travel bans), financial losses, vaccination mandates, and associated societal divisions.^4^

When examining the psychosocial impacts in a pandemic context, researchers experience key challenges not only with the choice of study design and measures but also in providing a multicultural perspective.^5^ In this respect, researchers have obtained data using convenience^6 7^ or representative sampling^8^ by employing either cross-sectional^8^ or longitudinal^7 9^ design. Those studies have been carried out either on the general population^6–8^ or on potentially vulnerable populations (such as the health workforce^10–12^ or those with pre-existing risk factors such as having a previous history of mental disorders^9 13 14^). Most studies include self-report measures of well-being, psychological distress, depression, anxiety and post-traumatic stress disorder (PTSD).^15^ However, these standardised measures do not examine the particular impacts of COVID-19-related stressors and there has been a call for novel COVID-19-specific measures to be used alongside established psychometric scales.^16^ In response, several COVID-19-specific scales have been developed which vary in focus and length. For example, one scale assesses fear associated with COVID-19 infection^17^ (see also Akan^6^), while another one examined a wide range of impacts of the pandemic and public health restrictions on physical health, employment and finances, and family and social disruption.^18^ Notably, the latter scale, in attempting to capture the wider psychosocial impacts, frequently reflects the context and country in which they were developed, limiting their more general applicability in other contexts. Researchers have also attempted to develop and validate brief screening tools for clinical research and practice; e.g., the 5-item Coronavirus Anxiety Scale^19^ and the 7-item COVID-19 Anxiety Scale.^20^ In addition, while the positive outcomes of the pandemic have been recognised,^21^ few studies formally assessed the positive impacts,^22 23^ which may limit a comprehensive understanding of the psychosocial impacts of COVID-19.

To date, the majority of the literature examining the psychosocial impacts of COVID-19 is from studies conducted in China, Europe and the USA and a few multinational studies have been carried out among the general population. A multinational study that examined the psychosocial impacts of COVID-19 across several high-income countries (HICs) found generalised anxiety among 21.0% and major depression among 25.5% of their respondents.^24^ Another study that examined the psychological impacts of COVID-19 across several HICs and low- and middle-income countries (LMICs), reported high rates of anxiety (28.2%), stress (18.3%) and depression (26.6%) in their community-based samples^25^ (see also^26^ for depression prevalence in LMICs). Some multinational studies have reported significant differences in these psychological impacts across countries.^26 27^ In comparison, studies investigating the psychosocial impacts in other regions, especially in LMICs are scarce, despite many of these areas being severely affected by COVID-19. The difficulties in evaluating the pandemic-related psychological impacts in these regions are compounded by the lack of standardised measures in the local languages of these countries, the absence of which limits the comparison of results between countries.

To address the issues identified above, we developed the 50-item COVID Psychosocial Impacts Scale (CPIS) to comprehensively assess the impacts of the pandemic including the adverse personal, social and economic consequences that followed. The construction of the scale was informed by our team’s experience assessing the psychosocial impacts of the Canterbury Earthquakes^28 29^ and the Mosque Attacks in 2019.^30^ Notably, the existing pandemic-related scales were also consulted in scale development.^6 16–20^ The items and subscales of CPIS were modelled on the Social Readjustment Scale^31^ assessing exposure to pandemic-related life events (disruptions to personal, family, employment, faith, education and daily routines) and the resultant level of stress. It also included questions examining the potential positive consequences of the COVID-19 pandemic. The CPIS was refined using the ‘group mind’ process,^32^ with colleagues from a range of countries and cultures (Bangladesh, Ghana, Pakistan and Turkey) reviewing a draft of the questionnaire, with iterative improvements based on their comments. The applicability of the CPIS for use in a range of countries and cultures was duly considered through collaboration with international colleagues.

The 50-item CPIS has been validated in a non-representative New Zealand sample at two-time points (2020, 2022) when the population exposure to COVID-19 community infections varied markedly.^33^ In that study, the CPIS was administered with a measure of psychological distress (Kessler Psychological Distress Scale, K10)^34^ and well-being (WHO Well-Being Index, WHO-5).^35^ Findings indicate a unidimensional structure within CPIS subscales while it correlates with psychological distress and general well-being is not only a proxy for these constructs.^33^ Based on findings from the validation study, we found that some items were less important in future iterations of the CPIS. Therefore, we have refined CPIS from 50 to 32 items.

In addition to developing the CPIS, the research team took the opportunity to use resources that had already been deployed for the translation of the research instruments for the March 15th Project^30^ to develop the CPIS into several different language versions (Arabic, Indonesian, Malay, Persian, Somali, Turkish and Urdu). To ensure that translations captured psychometric meanings in a culturally appropriate way, translations were carried out by proficient bilingual research assistants and interpreters who were familiar with the content and context, using parallel and back-to-back translations in an iterative process. These translations were then compared for internal consistency and examined for face validity.

Our planned programme of work is to examine the 32-item CPIS and translated psychometric measures in the countries of interest. This protocol describes a cross-sectional observational study to assess the psychosocial impacts of the COVID-19 pandemic in seven LMICs (Indonesia, Iran, Iraq, Malaysia, Pakistan, Somalia and Turkey). It uses an online survey that includes the 32-item CPIS and standardised measures of psychological distress, post-traumatic stress, well-being and post-traumatic growth. Our findings will increase our understanding of the psychosocial impacts of the COVID-19 pandemic across several LMICs with differing rates of infection, morbidity and mortality. Findings will also provide psychometric evidence on the novel CPIS. As a result, our research will contribute to a growing body of mental health measures that can be used for cross-cultural comparison.

## Methods and analysis

### Study design

This is a cross-sectional observational study examining the psychosocial impacts of the COVID-19 pandemic being conducted in seven LMICs.

### Measures

The measures have all been translated into the appropriate language for the country in which they will be administered (see online supplemental file). They include the following.

10.1136/bmjopen-2022-067886.supp1Supplementary data

#### Sociodemographic measures

Sociodemographic measures include age, gender, marital status, religion, ethnicity, self-reported English proficiency, highest level of education, occupation, study or work status and monthly income (in local currency). On the recommendation of the international collaborators, some of the demographic questions may vary to ensure contextual appropriateness. For example, in Turkey, students do not study part-time so that option was removed from the item.

#### Prior trauma exposure

The exposure to previous trauma will also be sought to examine the effect of previous trauma on the psychosocial impacts of COVID-19. Participants will be asked to select as many as appropriate from a list of previous exposure to natural disasters, war or military conflict, childhood adversity, physical or sexual assault, and serious physical accident.

#### COVID Psychosocial Impacts Scale

This is a novel 32-item measure used to examine the psychosocial impacts of the COVID-19 pandemic. The scale asks participants if they have experienced stressors in response to COVID-19 and then to indicate the magnitude of stress on a 6-point scale scored from 0=‘no’, 1=‘yes, no stress at all’ to 5=‘yes, a lot of stress’. An overall pandemic-related stress score can be calculated ranging from 0 to 160.

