#### Psychometric analyses

Reliability analyses will be carried out on each measure to determine the suitability of its use, employing item-total correlations and Cronbach’s α as a measure of internal homogeneity and consistency. The construct validity of CPIS with WHO-5 and K10 will be examined using a correlation matrix.

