#### Within-subjects analyses

Descriptive analysis will be carried out on sociodemographics (e.g., age, gender, ethnicity, religion, marital status, the highest level of education, work status, monthly household income, exposure to previous trauma) and study variables (well-being, psychological distress, post-traumatic stress, post-traumatic growth, pandemic-related stress from the CPIS) to inform site-specific sociodemographic profile and psychosocial outcomes. To explore the relationship between sociodemographic and study variables, follow-up analyses will be carried out using a linear mixed model (also known as multi-level modelling) to pool predictor variables. This will be carried out for each of the seven sites individually.

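### Cronbach's alpha and item-total correlations are the plan's suitability test for the CPIS, but they cannot show that 32 items from several life-event domains form the one scale that a 0–160 total implies

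*Protocol article*

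**What the plan says.** All references are to the protocol article.

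- **COVID Psychosocial Impacts Scale.** The instrument has 32 items, each scored 0 when the event was not experienced and 1 to 5 by rising stress when it was. The score defined is: "An overall pandemic-related stress score can be calculated ranging from 0 to 160". No subscale score is defined here.
- **Introduction.** The CPIS has subscales, and its items cover several areas of life, from work and study to family and faith. On structure, the earlier validation is summarised as: "Findings indicate a unidimensional structure within CPIS subscales". That validation used the 50-item version in a non-representative New Zealand sample. The scale was shortened afterwards: "Therefore, we have refined CPIS from 50 to 32 items". Translated versions of it are used in the seven countries.
- **Psychometric analyses.** "Reliability analyses will be carried out on each measure to determine the suitability of its use, employing item-total correlations and Cronbach’s α". Construct validity is a correlation matrix of the CPIS with WHO-5 and K10. No check of dimensionality is named.
- **Within-subjects analyses.** The CPIS appears in the list of study variables as one entry, "pandemic-related stress from the CPIS".

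**The concern.** One dimension within each subscale does not imply one dimension across all subscales. The reported evidence also concerns a longer instrument in another population. The article reports nothing on structure for the 32-item form in any of the seven countries.

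The planned check does not fill this gap. Alpha depends on the number of items and the average inter-item correlation. A long total can therefore have a high alpha even when its parts are only weakly related. Corrected item-total correlations are lifted in the same way by an item's close neighbours in its own subscale. The correlations with WHO-5 and K10 describe how the score relates to other constructs, not how its items relate to each other.

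Followed as written, the rule could declare the 0–160 total suitable in a country where it is not one scale. Two countries could then share a CPIS mean while having quite different profiles, and nothing in the planned psychometrics would show it. This matters because the Discussion presents two things as the study's contribution: cross-cultural comparison of personal, social and economic consequences, and formal psychometric evidence on suitability.

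**Working it through.** **Stated range.** 32 × 0 = 0 and 32 × 5 = 160, so the article's range reproduces and all 32 items enter the sum.

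**Inputs.** The number of items, n = 32, is from the article. The number and size of subscales and all inter-item correlations are assumptions, because the article gives none. Let each of k equal subscales have m items, with inter-item correlation w within a subscale and b between subscales.

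**Formulas.**
- Sum of the item correlation matrix: S = n + n(m − 1)w + n(n − m)b
- Standardised alpha = n/(n − 1) × (1 − n/S)
- Corrected item-total r = c/√(S − 1 − 2c), where c = (m − 1)w + (n − m)b
- Correlation of two subscale scores = m²b/(m + m(m − 1)w)
- Share of total-score variance due to a general factor = n²b/S

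**Example A: four subscales of 8, w = 0.40, b = 0.05.**
- S = 32 + 32×7×0.40 + 32×24×0.05 = 32 + 89.6 + 38.4 = 160 (that this equals the maximum score is coincidence)
- Alpha = 32/31 × (1 − 32/160) = 0.826
- c = 2.8 + 1.2 = 4.0, so item-total r = 4/√151 = 0.326
- Subscale correlation = 3.2/30.4 = 0.105
- General-factor share = 51.2/160 = 0.32

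**Example B: four subscales of 8, w = 0.30, b = 0.10.**
- S = 32 + 67.2 + 76.8 = 176
- Alpha = 32/31 × (1 − 32/176) = 0.845
- c = 2.1 + 2.4 = 4.5, so item-total r = 4.5/√166 = 0.349
- Subscale correlation = 6.4/24.8 = 0.258
- General-factor share = 102.4/176 = 0.58

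**Range over other structures (w from 0.3 to 0.6).**

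| Structure | b = 0: alpha | b = 0: item-total r | b = 0.1: alpha | b = 0.1: item-total r | b = 0.1: general-factor share |
|---|---|---|---|---|---|
| 2 × 16 | 0.845–0.929 | 0.349–0.519 | 0.887–0.943 | 0.417–0.567 | 0.276–0.451 |
| 4 × 8 | 0.699–0.834 | 0.217–0.335 | 0.845–0.896 | 0.349–0.436 | 0.421–0.582 |
| 8 × 4 | 0.489–0.664 | 0.118–0.195 | 0.813–0.848 | 0.310–0.354 | 0.571–0.681 |

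**Reading.** The article sets no cut-offs. I take the common conventions of 0.70 for alpha and 0.30 for item-total r. At b = 0.1 every structure passes both, although a common factor carries only 28% to 68% of the variance of the total. At b = 0, where there is no common scale at all, two 16-item subscales still pass both. Four 8-item subscales give alpha from 0.70 upward, though their item-total r can fall below 0.30. Both statistics clearly fail only for eight small, uncorrelated subscales.

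**The case against.** Several points on the other side are sound.

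- **The article does not confine the CPIS to one total.** A reader might infer this, but the wording only says that a total can be calculated. The Discussion also mentions the number of exposures, and the between-subjects section speaks of pandemic-related variables in the plural. The single entry in the within-subjects list proves little, since post-traumatic growth is also one entry there although its inventory has five named subscales.
- **Subscale alphas are not excluded.** Reliability for each measure does not rule them out. It does not call for them either.
- **The validation may say more.** A reader might infer that it supports one dimension only within subscales. The article does not say only, and the validation paper is not at hand.
- **A total can be defended.** The scale is modelled on a life-event instrument, and a cumulative-burden index need not be unidimensional. This stands. But the article does not make that argument, and alpha and item-total correlations are not the right suitability criteria for such an index. On either reading, the score and its check do not match.
- **Life role.** It is tempting to say that respondents without work or study have a lower ceiling, which would distort associations with work status. If 6 of the 32 items concerned work or study, the ceiling would be 160 − 6 × 5 = 130. The article allocates no items to domains, so the 6 is invented for illustration. Under an index reading, a zero there correctly records no exposure. Work status is also collected and can be adjusted for.
- **An article condenses.** Scoring detail may sit in a fuller document. The point here is therefore not missing detail. It is that the suitability criterion the article does state cannot answer the question put to it.

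**Conclusion.** The point holds in a limited form. The article defines a 0–160 total, reports structural evidence within subscales for a longer version of the scale, and decides suitability by statistics that do not test whether the 32 items form one scale. Under plausible assumed structures, a total whose subscales correlate at 0.11 to 0.26 would pass with alpha of 0.83 to 0.845 and item-total r of 0.33 to 0.35. The size rests wholly on assumed subscale counts and correlations.

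The documents do not show that the total is invalid, that the planned analysis is wrong, or that alpha could never reveal a problem. With many small, nearly uncorrelated subscales it would. This is a worthwhile and cheap improvement to the psychometric section. It concerns how the CPIS total may be interpreted.

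**What to change.** In the psychometric analyses:

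1. State which items belong to which CPIS subscale, and compute alpha and item-total correlations within each subscale, by country.
2. Report the inter-subscale correlation matrix for each country.
3. Fit a one-factor or bifactor model to the 32 items.
4. Report subscale scores alongside the 0–160 total.
5. State the rule for the total: interpret it as a scale only where these results support that. Otherwise present it as a cumulative-exposure index, for which alpha is not the suitability criterion.

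No new data are needed, because every item is already in the survey. This matters since recruitment is complete in five of the seven countries. The cost is some wording, a few more tables, and several CPIS results per country instead of one.

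Two further steps are optional: making the subscales primary in place of the total, and restricting employment and education items to respondents whose recorded work or study status makes them applicable.

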#### Kessler-10

This is a 10-item measure assessing symptoms of psychological distress in the previous 30 days.^34^ Each item is scored from 1=‘none of the time’ to 5=‘all of the time’. The raw score can range from 10 to 50; with scores 30 and above indicating severe mental distress.^36^

#### WHO Well-Being Index

This is a short 5-item measure assessing subjective psychological well-being in the previous 2 weeks.^35^ Each item is scored from 0=‘at no time’ to 5=‘all of the time’. The raw score range is 0–25; this can be multiplied by 4 to give a final score, with 100 representing the highest subjective well-being rating.

#### PTSD Checklist for DSM-5

This is a 20-item measure assessing symptoms of PTSD in the past month anchored in response to COVID-19 as a potentially traumatic event. Each item is scored from 0=‘not at all’ to 4=‘extremely’; with a severity score range of 0–80.^37^

#### Post-traumatic Growth Inventory

This is a 21-item measure assessing change following exposure to trauma,^38^ adapted to reflect how change occurred in your life as a result of COVID-19. There are five subscales (relating to others, new possibilities, personal strength, spiritual change and appreciation of life). Each item is scored from 0=‘not at all’ to 5=‘a lot’ with a score range of 0–105, with higher scores reflecting positive transformation after the traumatic event.

### Participants

Adults (aged 18 years and over) who reside in Indonesia, Iran, Iraq, Malaysia, Pakistan, Somalia or Turkey will be recruited as participants. Anyone aged below 18 years and those not currently residing in the country of interest will be excluded from the study.

